## Abstract

**Background:**

Gut microbiota (GM) might play a role in muscle metabolism and physiological processes through a hypothesized gut-muscle axis, influencing muscle mass and function and thus, sarcopenia. The Trial in Elderly with Musculoskeletal Problems due to Underlying Sarcopenia—Faeces to Unravel the Gut and Inflammation Translationally (TEMPUS-FUGIT) aims to explore the gut-muscle axis in sarcopenia.

**Methods:**

First, in a cross-sectional case–control phase, 100 community-dwelling adults without sarcopenia will be compared to 100 community-dwelling adults (≥ 65 years) with sarcopenia of similar age-, gender and BMI-ratio, participating in the ongoing ‘Exercise and Nutrition for Healthy AgeiNg’ (ENHANce; NCT03649698) study. Sarcopenia is diagnosed according to the European Working Group on Sarcopenia in Older People 2 (EWGSOP2) criteria. GM composition and intestinal inflammatory markers (fecal calprotectin, lactoferrin and S100A12) will be determined in fecal samples. Systemic inflammatory markers (hs-CRP, IL-4, IL-6, TNF-α, IL-13, IL-1β and creatine kinase) will be determined in fasted blood samples. Both groups will be compared using appropriate statistical testing, whereas linear regression will be used for cross-sectional associations between gut, inflammatory and sarcopenia parameters.

Second, in the longitudinal phase, sarcopenic older adults will be requested to deliver five fecal samples during the 12-week intervention to assess the effects of protein, omega-3 and a physical exercise program on the GM.

**Discussion:**

TEMPUS-FUGIT aims to explore the gut-muscle axis by comparing GM composition between sarcopenic and non-sarcopenic older adults and to determine the association of GM with intestinal and systemic inflammatory markers and sarcopenia-defining parameters (muscle mass, muscle strength and physical performance). Furthermore, effects of single or combined, optimized and individualized anabolic interventions (exercise, protein and omega-3 supplementation), on GM will be explored in persons with sarcopenia.

TEMPUS-FUGIT aims to impact clinical practice by clarifying the relationship between the gut-muscle axis and sarcopenia. TEMPUS-FUGIT is expected to contribute to the discovery of clinical and microbial biomarkers for sarcopenia and insights in its pathophysiology, opening possible future perspectives for novel sarcopenia treatment strategies targeting GM.

**Trial registration:**

ClinicalTrails.gov NCT05008770, registered on August 17, 2021; first participant enrolled on September 21 2021.

**Supplementary Information:**

The online version contains supplementary material available at 10.1186/s12877-023-04291-5.

## Background

Sarcopenia is a progressive skeletal muscle disorder characterized by the age-related loss of muscle mass and function, leading to ‘muscle failure’. When no other factors than aging trigger the muscle loss, sarcopenia is considered ‘primary’ [1–4]. Sarcopenia is highly prevalent and predisposes older adults to deleterious health outcomes such as disability, mobility limitations, fractures and mortality [5–9].

Previous research has linked altered gut microbiota (GM) with inflammatory and age-related diseases such as Alzheimer’s disease and Morbus Parkinson [10]. GM are an overall resilient but complex ecosystem of viruses, fungi, parasites, yeasts and bacteria, symbiotically living in the human intestine, reaching peak diversity and richness in the colon [11–13]. The composition of the GM rapidly changes before the age of 3 years, stabilizes in adulthood and alters with aging [14]. Healthy GM regulate physiological processes through several mediators i.e. Short Chain Fatty Acids (SCFA), antioxidants and cytokines [12]. Normal aging is associated with decreased biodiversity and overgrowth of pathobionts, defined as ‘dysbiosis’, leading to a decrease of the aforementioned mediators [15].

Recent studies suggest that GM also play a role in muscle metabolism and physiology through a hypothesized ‘gut-muscle axis’, directly influencing muscle mass and function and hence, sarcopenia. However, some gaps in the literature regarding this gut-muscle axis remain and urge further investigation.

First, prior studies generally reported decreased GM diversity in sarcopenic persons and older adults with low muscle mass compared to respectively non-sarcopenic persons and older adults with normal muscle mass [16–18]. However, inconsistent associations were reported between GM and sarcopenia-defining parameters (muscle mass, muscle strength and physical performance); in addition, various sarcopenia definitions were used in studies that investigated the GM composition of persons with sarcopenia.

Second, disturbed GM might influence the age-related chronic low-grade systemic inflammation or ‘inflammaging’ in older persons, a major driving mechanism behind sarcopenia [19, 20]. Dysbiosis also results in chronic intestinal inflammation. However, data about intestinal inflammation as well as data on the association between GM and both systemic and intestinal inflammation in persons with primary sarcopenia are lacking [21]. In patients with Inflammatory Bowel Disease (IBD), in whom the incidence of sarcopenia is 42%, sarcopenia is associated with altered GM and increased levels of the gut inflammatory markers fecal calprotectin, lactoferrin and S100A12 [22–25]. However, similar data in older adults with primary sarcopenia are lacking.

Third, whereas GM might influence the pathophysiology of sarcopenia, recommended treatments for sarcopenia, i.e., protein supplementation and physical exercise, may, in turn, alter the GM. However, not all data are consistent with a beneficial effect of physical exercise and a high-protein diet on GM. To illustrate, protein supplemented athletes expressed decreased health-related GM, but their levels of health-related mediators, such as SCFA were unchanged [26]. Also, young adults acutely exposed to high levels of physical training expressed increased opportunistic gut pathogens (e.g., Streptococcus) and a pro-inflammatory profile [27, 28]. Nonetheless, results are conflicting, and no data are available regarding the effect of sarcopenia treatment on GM composition in older adults with primary sarcopenia.

The Trial in Elderly with Musculoskeletal Problems due to Underlying Sarcopenia-Faeces to Unravel the Gut and Inflammation Translationally (TEMPUS-FUGIT) aims to unravel the gut-muscle axis in age-related sarcopenia by addressing these gaps. First, TEMPUS-FUGIT will compare GM composition and intestinal inflammation between a well-defined sarcopenic community-dwelling older population and non-sarcopenic controls. Second, in sarcopenic individuals, associations between sarcopenia-defining parameters and GM, systemic and intestinal inflammation, that all may contribute to sarcopenia, will be explored. An overview of the associations that will be investigated is given in Fig. 1. Finally, TEMPUS-FUGIT will explore the effects of optimized and individualized anabolic treatments for sarcopenia on the GM composition and intestinal inflammation in older persons with sarcopenia. We hypothesize a significant effect of these anabolic interventions on the GM composition in sarcopenic persons.

**Fig. 1 Fig1:**
[figure not shown]
TEMPUS-FUGIT: Exploring the gut-muscle axis in sarcopenia. * Gut microbiota, intestinal and systemic inflammation may contribute to development of sarcopenia

## Methods/design

### General design

The TEMPUS-FUGIT-project is a single center study conducted in the University Hospitals (UZ) Leuven, Leuven, Belgium. The study set-up is two-fold, consisting of an observational, cross-sectional, case–control phase and a longitudinal, interventional, phase.

In the cross-sectional study phase, the primary objective is to compare GM composition and intestinal inflammatory markers between 100 healthy community-dwelling older adults without sarcopenia and 100 community-dwelling older adults with sarcopenia.

The longitudinal phase of TEMPUS-FUGIT has a triple-blinded randomized controlled trial (RCT) set-up. This comprises a 12-weeks program of single or combined, optimized, and individualized anabolic interventions (a physical exercise program, protein and/or omega-3 polyunsaturated fatty acids (PUFA) supplementation). The effects of these interventions on GM composition and fecal intestinal inflammatory markers will be assessed in 100 sarcopenic older adults. To this end, participants will be 1:1 allocated into one of five intervention groups, which differ in the combination of the exercise and nutritional interventions.

An overview of the general set-up of the TEMPUS-FUGIT study is given in Fig. 2. More details on the interventions have been previously published by Dedeyne et al. and will be summarized further in this manuscript [29].

**Fig. 2 Fig2:**
[figure not shown]
TEMPUS-FUGT general study design PUFA: Polyunsaturated Fatty Acid, EWGSOP2: European Working Group on Sarcopenia in Older People 2

### Participants

In TEMPUS-FUGIT 100 healthy community-dwelling non-sarcopenic older adults (aged ≥ 65 years) will be recruited to be compared with 100 older adults with sarcopenia defined according to the revised definition of the European Working Group on Sarcopenia in Older People (EWGSOP2) [30]. The sarcopenic older adults will also participate in the longitudinal (interventional) phase of the study.

The sarcopenic and the non-sarcopenic group will be gender-matched, whereas for age and Body Mass Index (BMI), caliper matching (maximum tolerated difference between matched persons) will be applied [31]. Sarcopenic older adults will be recruited from the ongoing triple blinded RCT ‘Exercise and Nutrition for Healthy AgeiNg’ (ENHANce) study (Clinical Trial number NCT 03649698) [29]. Participants will be recruited from the environment of Leuven, Flanders, Belgium. To ensure recruitment of a sufficient number of study persons, contacts have been established with the geriatric outpatient clinic (including falls prevention clinic) and representatives of service flats and day care centers or organizations for older adults. Furthermore, medical staff collaborating to the project will use their network for recruitment. Also health care specialists, i.e., general practitioners, pharmacists and physiotherapists will be requested to refer patients who may be eligible for this study. Also information about the study will be distributed by organizations and websites that target older persons, advertisements in local newspapers and distributions of flyers. Older adults, who were initially screened for the ENHANce study but failed to meet the inclusion criteria for sarcopenia, will be re-contacted to participate in the non-sarcopenic control group of the TEMPUS-FUGIT study.

### Assessment of eligibility criteria

Sarcopenic participants should be diagnosed with probable (low muscle strength), confirmed (low muscle strength & mass) or severe sarcopenia (low muscle strength, mass and physical performance) by EWGSOP2 [30], whereas healthy controls should not have sarcopenia. Furthermore, controls as well as sarcopenic participants should meet the following inclusion criteria: ≥ 65 years, community-dwelling or assisted living, able to communicate in Dutch both orally and written, have a Mini-Mental State Examination (MMSE) Score ≥ 21 points, be in the possession of a freezer for preservation of fecal samples, absence of diabetes and no intake of diabetes medication, no intake of corticoids, absence of terminal illness with prognosis < 6 months, no antibiotics use in the past 3 months, absence of ongoing or previous (< 5 years) malignancy of the gastrointestinal tract, no Irritable Bowel Syndrome (IBS) or IBD, no chronic kidney disease (glomerular filtration rate (eGFR) < 30 ml/min/1.73m^2^) and absence of disorders, recent complaints, injury or surgery that prevent participation to the study according to the researchers. Additionally, sarcopenic participants should not have followed a rehabilitation or physical exercise program > 2/week in the last six months and should have a protein intake ≤ 1.5 g per kg body weight (BW) per day.

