When the participant does not meet the EWGSOP2-criteria for (probable) sarcopenia, the participant will be included as a non-sarcopenic control person in the cross-sectional phase of the TEMPUS-FUGIT study. Non-sarcopenic participants will follow the same preparation period as described above, being requested to complete food diaries and health questionnaires, to collect two stool samples and wear the IMU, but without being block randomized to the interventions (nutritional supplementations and/or the exercise program).

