
### Sample size

In TEMPUS-FUGIT, a pragmatic sample of 100 sarcopenic people from the longitudinal phase, will be compared with 100 non-sarcopenic volunteers. Therefore, 110 non-sarcopenic controls will be recruited, in order to ensure 100 included control persons that, similarly to the sarcopenic participants, have a protein intake < 1.5 g/kg BW/day. Indeed, based on previous similar data, we expect, a drop-out of 5.88% in the non-sarcopenic control group due to a protein intake > 1.5 g/kg BW/day, [58]. Due to the exploratory character of this study, no sample size calculation was performed. Based on previous studies, 100 participants in each group is considered as sufficient for this study [16, 18, 29].

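### The limit on prior exercise programmes binds cases but not controls, building a selection difference into the case–control comparison; the protein limit for controls is stated inconsistently

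*Protocol article*

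**What the plan says.** All references are to the protocol article.

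- **Assessment of eligibility criteria, common list.** It opens with "controls as well as sarcopenic participants should meet the following inclusion criteria". It contains neither an exercise limit nor a protein limit.
- **Same section, cases only.** "Additionally, sarcopenic participants should not have followed a rehabilitation or physical exercise program > 2/week in the last six months". The same sentence adds that cases "should have a protein intake ≤ 1.5 g per kg body weight (BW) per day".
- **Preparation period, route into the control group.** "When the participant does not meet the EWGSOP2-criteria for (probable) sarcopenia, the participant will be included as a non-sarcopenic control person". No exercise or protein condition is named there.
- **Sample size.** 110 controls are to be recruited "in order to ensure 100 included control persons that, similarly to the sarcopenic participants, have a protein intake < 1.5 g/kg BW/day", allowing for "a drop-out of 5.88% in the non-sarcopenic control group due to a protein intake > 1.5 g/kg BW/day".
- **Participants.** Groups are matched on gender, with calipers for age and BMI. Neither activity nor protein intake is a matching variable.
- **Background.** The recommended treatments, "protein supplementation and physical exercise, may, in turn, alter the GM". The same paragraph calls the results conflicting.
- **Preparation period, measurements.** Controls as well as cases keep food diaries and wear the activity monitor. The monitor goes on five days before the baseline visit.

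**The concern.** In a case–control comparison, a selection rule should act on both groups unless it defines the case. Programme participation does not define sarcopenia. The limit has an obvious purpose for the randomised phase, where some arms receive exercise, but the same cases also serve the cross-sectional phase. There the rule removes people with sarcopenia who have recently trained more than twice a week and keeps comparable people without sarcopenia. A difference in diversity, enterotype or taxa could then partly reflect recent training. The direction of any such bias is unknown, because the Background itself reports mixed evidence.

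The protein limit raises a different problem. The eligibility and Preparation period sections would admit a control with a high protein intake, and the Sample size section would remove the same person. Two people applying the article would assemble different control groups.

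**Working it through.** **1. The plan's own figure.** The inputs from Sample size are 100 controls to retain and a 5.88% loss for protein.
- Needed: 100 / (1 − 0.0588) = 106.2, so 107. The plan recruits 110.
- Expected to remain: 110 × (1 − 0.0588) = 103.5.

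So 110 covers the stated loss. Excluding high-protein controls is a working part of the recruitment target.

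**2. The two criteria side by side.**

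| Criterion | Cases | Controls: eligibility and Preparation period | Controls: Sample size |
|---|---|---|---|
| Programme > 2/week in six months | excluded | no limit | no limit |
| Protein, g/kg BW/day | ≤ 1.5 | no limit | < 1.5 |

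Exercise is one-sided throughout the article. Protein is contradictory. The boundary also varies: ≤ 1.5 for cases, < 1.5 for retained controls, and > 1.5 as the reason for loss. A control at exactly 1.5 is neither retained nor counted as lost.

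**3. Size of the protein contradiction.** 110 × 0.0588 = 6.5, so about 6 of the controls recruited. If the eligibility list were followed literally, 5.88% of controls would exceed the limit. With an assumed effect of 0.2–0.8 SD in those people, the group shift is 0.0588 × 0.2 = 0.012 SD to 0.0588 × 0.8 = 0.047 SD. By the formula in step 4, the false-positive rate is 5.1–6.3%.

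**4. Size of the exercise difference.** The documents give neither the share of controls above the limit nor an effect, so both are assumed. The share among cases is zero by rule.
- Shift: b = share × effect.
- Rejection probability with no sarcopenia effect, 100 per group, two-sided 5% (sidedness assumed): Φ(b/SE − 1.96) + Φ(−b/SE − 1.96), with SE = √(2/100) = 0.1414 SD.

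| Assumed share | Assumed effect (SD) | Shift b (SD) | False positives |
|---|---|---|---|
| 20% | 0.3 | 0.06 | about 7% |
| 20% | 0.5 | 0.10 | about 11% |
| 30% | 0.5 | 0.15 | about 19% |
| 40% | 0.5 | 0.20 | about 29% |

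Widening the assumptions to shares of 10–50% and effects of 0.2–0.8 SD gives shifts of 0.02–0.40 SD and false-positive rates of 5.2–81%. The result is governed by the assumptions.

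**5. Can adjustment repair it?** Not fully. No eligible case exceeds the exercise limit, so among participants above it there is nobody with sarcopenia to compare. A covariate for participation above the limit would rest entirely on the model. The activity monitor covers days before baseline, not six months of programme attendance.

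**6. Cost of restricting controls.** If 20–40% exceed the limit, 103.5 × 0.8 = 82.8 or 103.5 × 0.6 = 62.1 controls remain. The difference detectable with 80% power (assumed) against 100 cases is 2.80 × √(1/100 + 1/n):
- n = 100: 0.40 SD
- n = 83: 0.42 SD
- n = 62: 0.45 SD

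**The case against.** A reader might infer that the groups differ by design on two determinants of the microbiota, exercise and protein. The documents do not support this for protein. The Sample size section intends controls to be limited as cases are and sizes recruitment accordingly. That part is an inconsistency between sections, and its numerical effect is small.

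Other objections have weight:

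- **The rule is narrow.** Only programmes above twice a week are excluded. Cases who exercise up to that level remain, so it would be wrong to say that all regular exercisers are removed from the case group.
- **Low activity may belong to sarcopenia.** Less active controls would also be less representative of older adults without the condition. This is a fair reason not to match on activity in general. It does not explain excluding trained cases while keeping trained controls, which is a product of the trial's recruitment and not of the disease.
- **Adjustment may be planned.** The article names adjustment for the association models, with age as its example, and gives no covariate set for the group comparison. Such a set may stand in an analysis plan not shown, so it cannot be said that the comparison will be unadjusted. Diaries and activity data exist in both groups. Step 5 of the working limits what they can achieve for this criterion.
- **The false-positive figures are for one index.** The primary outcomes are several indices, enterotypes, cell counts and taxa, analysed with non-parametric tests, PERMANOVA and LEfSe, with false discovery rate control. The 7–29% does not carry over directly.

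**Conclusion.** The point holds for exercise. As written, the plan builds a difference in recent structured exercise into the primary case–control comparison. Matching does not remove it, and adjustment can repair it only in part. Whether it matters in practice depends on how many controls exceed the limit and on whether exercise at that level shifts the microbiota in this population. The documents give neither, so the 0.06–0.20 SD and 7–29% are illustrations. At the low end the harm is slight. It would go too far to conclude that any observed difference must be due to exercise.

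For protein, the finding is a contradiction about who is an eligible control, including a boundary that differs between sections. It should be corrected before the control group is finalised, but it is not a demonstrated group difference.

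The change is advisable, because it removes an avoidable alternative explanation at modest cost.

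**What to change.** 1. Reconcile Assessment of eligibility criteria, Preparation period and Sample size, so that one protein rule with one boundary applies to cases and controls. Which boundary to use is for the sponsor to decide.
2. Apply the exercise-programme criterion to controls still to be enrolled. At the least, record participation over the preceding six months in all controls, including those already enrolled. One question is enough, if the health questionnaire does not already ask it.
3. Pre-specify a case–control analysis restricted to controls who meet both case criteria, and report it beside the analysis of all controls. Agreement would support attributing a difference to sarcopenia; disagreement would show how far the selection rule matters.

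**Cost.** A short amendment and one added question; food diaries are already collected in both groups. The restricted analysis would use fewer controls, about 62–83 of the expected 103.5 on the assumed shares. The detectable difference would rise from 0.40 to about 0.42–0.45 SD, and some matched controls would be lost. For this reason the restricted analysis is proposed alongside the all-controls analysis and not in its place. If the criterion is applied at enrolment, the target of 110 may need a further allowance, which the documents do not permit to be calculated.

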### Study procedures

#### Screening visit

TEMPUS-FUGIT starts with a screening visit, where study procedures will be explained, eligibility criteria will be checked and informed consent will be obtained by one of the researchers. If the participant qualifies for the study, weight (SECA, model no 8801321009, SECA UK Ltd.) will be measured to the nearest 0.1 kg and height (Harpenden stadiometer Holtain Ltd., Crosswell UK) to the nearest 0.1 cm, measured barefoot, standing upright with clothes on. BMI is calculated through weight/height^2^ (kg/m^2^). Hand grip strength (HGS) will be measured with a handheld dynamometer (Jamar 1, TEC Inc., Clifton, NJ, USA) while the participant is seated, holding the arm in a 90° angle. According to the Southampton protocol, HGS is measured six times for alternating hands and the maximal value is reported [32, 33]. The chair stand test (CST) determines leg muscle strength by measuring the time it takes for the participant to rise five successive times out of a chair as fast as possible without using any support and holding the arms crossed in front of the chest. Cut-off values for low muscle strength according to EWGSOP2 (and, hence, probable sarcopenia) are > 15 s for the CST for both sexes and a HGS < 27 kg and < 16 kg for men and women respectively [5]. Finally, when no recent lab results (12 weeks old) are available, an additional fasted sample will be taken in order to check whether the participants fasted glucose levels are < 126 mg/dl or HbA1C < 6.5%, to exclude diabetes mellitus [34].

